## Abstract

**Background:**

Women who experience intimate partner violence (IPV) are more likely to develop disabling chronic pain (CP). However, there is little information on what it means to live with CP while being exposed to IPV. In addition, despite well-established risk and protective factors for CP and its health outcomes, there are no data on whether these factors differ in women who have experienced IPV compared to those who have not.

**Objective:**

Our aims are to understand the meaning and implications of living with CP for women who have experienced IPV compared to women with CP alone and to identify possible differences in risk and protective factors as well as health outcomes.

**Methods:**

We have designed 2 studies to be conducted in 2 phases. The first phase will involve a qualitative study with a descriptive and exploratory design. Individual semistructured interviews will be conducted with at least 10 women with CP alone and with 10 women with CP who have experienced IPV. Reflexive thematic analysis will be used to examine participants’ experiences, meanings, and realities. In the second phase, a cross-sectional study will be conducted with women with CP affected by IPV, including those currently experiencing IPV and those with past exposure to IPV, as well as women with CP who have never experienced IPV. A total of 359 women will complete various scales assessing risk and protective factors (eg, pain-related worrying and activity patterns) and health outcomes (eg, legal and illegal drug use and health care use). Data analysis will involve inferential statistics and machine learning.

**Results:**

As of May 2025, we had contacted relevant associations to present the project and begin recruiting voluntary participants. We have conducted the pilot study to assure the adequacy of the questionnaire and usability or technical functionality of the web-based platform. The results are expected to be published starting in January 2026.

**Conclusions:**

This research addresses two urgent needs in pain research identified by the European Pain Federation: (1) expanding knowledge on CP management in relation to contextual factors; and (2) identifying specific psychosocial, self-management, and health profiles among women with CP who have experienced IPV and those who have not. This could provide valuable insights for personalizing pain management treatments. In addition, the findings may help identify women experiencing IPV who present to health care settings.

**International Registered Report Identifier (IRRID):**

PRR1-10.2196/66396

## Introduction

### Background

Chronic pain (CP) is defined as pain that persists beyond the normal tissue healing period, typically lasting approximately 3 months. It is a major health concern affecting approximately 30% of people worldwide [1]. CP is more prevalent and burdensome among populations experiencing vulnerability, including women, older adults, children, individuals from racial or ethnic minority groups, and those from lower socioeconomic backgrounds [2,3]. In Europe, the economic burden of CP could reach up to €300 billion annually (US $343 billion) [4].

There is broad consensus that understanding and treating CP requires a biopsychosocial approach. Beyond biological and physiological factors, psychological, social, and life experiences play a crucial role in the development, exacerbation, and persistence of pain [5-7]. Notably, CP is a well-documented consequence of another public health problem, intimate partner violence (IPV) against women, as demonstrated by controlled studies in both population-based and clinical samples [8-11].

IPV against women is a gender-based issue [12-14] that encompasses physical, psychological, or sexual violence perpetrated by some men against their female partners [15]. Today, IPV against women remains a widespread epidemic, affecting at least 30% of women worldwide [16]. It has severe health and social consequences [17] and imposes an economic cost of €174 billion (US $199 billion) per year on the European Union [18].

Compared to women who have not experienced violence, those exposed to IPV against women report a higher prevalence of fibromyalgia, abdominal pain, genitourinary tract pain, pelvic and genital pain, headaches (including migraines), and back and neck pain [19-22]. A study conducted with 108 male and female patients with CP attending a rehabilitation center found that 56% had a current or past history of IPV, with more than 80% being women. Nearly 30% had experienced IPV within the previous year [23].

Other studies have shown that those who have experienced IPV and are living with sickle cell disease are 5 times more likely to report CP than those who have never experienced IPV [24]. In addition, they are nearly twice as likely to develop fibromyalgia and chronic fatigue syndrome [25]. A recent systematic review and meta-analysis found strong and consistent associations between women who have experienced violence—whether by a partner or others—and CP conditions [26]. Furthermore, IPV against women is often linked to disabling pain [8,23,27]. Survivors with disabilities are more likely to report generalized CP than those with other disabling health conditions [28], and more than one-third continue to experience a high level of pain-related disability long after ending the abusive relationship [29].

Women who have experienced IPV also frequently use medication to alleviate pain [30]; for example, individuals with sickle cell disease who have experienced interpersonal violence are more than 6 times as likely to use opiate-based medications daily compared to those without a history of violence exposure [24].

Given the increased likelihood of those with exposure to IPV against women developing disabling CP and experiencing worse health outcomes [23,24,28,30]—even after leaving a violent relationship [29]—it is possible that experiencing (or having experienced) IPV against women influences the risk and protective factors involved in the development and maintenance of disabling CP differently. While previous studies have examined factors that predict or contribute to CP in those with exposure to violence [31,32], to our knowledge, no comparative studies have explored whether the underlying factors of CP differ based on a history of interpersonal violence.

Gathering this information is crucial for early detection and tailored treatment strategies for CP management in women who have experienced IPV as well as those who have not. Some researchers suggest that women with CP who are experiencing IPV may require more holistic care and support [26]. In addition, there is a need to better understand the daily experience of women living with CP while currently experiencing IPV compared to that of women who experience CP without a history of experiencing violence. However, no studies on this topic were found in the reviewed literature. In fact, the intersection of CP and IPV against women as interrelated phenomena has received little research attention [23].

### Goals of This Study

This research project has 2 general objectives and 6 specific aims.

First, we seek to understand the meaning and implications of living with CP for women experiencing IPV compared to those with CP alone. From this point forward, the term “women with CP alone” will refer to women who have never experienced any form of psychological, physical, or sexual violence at any stage of their lives, whether perpetrated by an intimate partner or another known or unknown individual. We include other forms of violence beyond IPV against women because they may also influence CP management and health outcomes [31].

More specifically, by comparing women with CP and exposure to IPV to women with CP alone, we aim to (1) examine how CP affects their daily lives, (2) identify the impact that CP may have on their intimate relationship and vice versa, (3) understand how they self-manage CP, and (4) describe their experiences with health systems.

Second, we aim to determine whether women with CP alone, women with CP who are currently experiencing IPV, and women with CP who have a past history of IPV present distinct profiles based on risk and protective factors for disabling CP and health outcomes. If differences exist, we will also (5) identify the factors that best explain these profiles and (6) detect more specific subprofiles within each group.

Ultimately, the findings will be used to develop assessment and intervention guidelines for health and social service professionals.

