### IPV Against Women: European Union Agency for Fundamental Rights Study on Violence Against Women Survey Inventory

Participants will complete an inventory [127] consisting of 32 items that assess various forms of violence exerted by a partner: 11 items on physical violence, 4 on sexual violence, and 17 on emotional and psychological violence. Participants will respond with the frequency of each type of violence (0=*never*, 1=*once*, and 2=*more than once*) and specify whether the violence was inflicted by a past or current partner, including the duration of the violent relationship. A woman will be classified as experiencing current IPV or having experienced past IPV if she reports experiencing any item more than once from the same partner.

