#### Participants

The reference population will include heterosexual women aged ≥18 years living in the province of Alicante. To detect possible differences in profiles, the study will be carried out in 3 groups of women: those who have CP and have never experienced IPV or any other type of violence (group 1), those who have CP and are currently experiencing IPV (group 2), or those who have CP and have a past history of IPV (group 3). It is important to note that the effects of violence may continue to impact individuals long after the relationship ends, and this study aims to identify risk and protective factors, as well as health outcomes, to support detection and intervention efforts.

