#### Variables and Instruments for Risk and Protective Factors

### Sociodemographic Characteristics

Age, belonging to a minority group (yes or no), years of education, annual household and personal incomes (categorized as €0 to €19,000; €20,000 to €40,000; and >€40,000; 1€=US $1.14), relationship status (single, partnered, or married), relationship duration (years), relationship satisfaction (10-point scale), CP diagnosis (yes or no), and time since CP diagnosis (years).

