#### Data Analysis

Inferential statistics help researchers draw conclusions about populations based on sample data, providing insights into social phenomena [153]. Machine learning, as a subset of artificial intelligence (AI) techniques, analyzes large datasets to identify patterns and make predictions [154]. These methods are transformative in gender studies, uncovering patterns in gender-related data and deepening the understanding of social inequalities and biases [155]. These methods have been successfully applied to areas such as forecasting gender-based violence, further demonstrating their relevance in social sciences [156].

Exploratory data analysis (EDA) will be crucial in examining CP and its connection to past or current IPV against women. EDA uses techniques such as scatterplots, clustering algorithms, and principal component analysis to investigate multidimensional datasets [157]. Scatterplots help identify correlations between sociodemographic variables, clustering algorithms reveal subgroups within the population, and principal component analysis reduces dimensionality to uncover latent factors such as the relationship between gender identity and social support [158]. The use of EDA will allow us to detect groups and subgroups at a glance by creating subclusters, that is, more specific profiles in each of the groups.

Inferential statistical methods will be applied to differentiate between women with CP alone and those with CP who have experienced IPV in the past or are currently experiencing IPV. Hypothesis testing, estimation, and prediction techniques will be used to make comparisons, with visual tools such as boxplots for examining variable distributions across groups. We will use 2-tailed *t* tests and ANOVA to compare means across groups [159].

Feature ranking techniques will help identify the most relevant variables for accurate classification. Methods such as information gain, gain ratio, Gini index, and relief will determine the importance of features such as education, socioeconomic status, pain level, and social support [160]. This feature ranking will help prioritize the most influential factors affecting each group, including those based on country distribution.

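### Group membership in phase 2 depends on lifetime history and so on age, but the stated t tests and ANOVA do not adjust for age

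*Protocol article*

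**What the plan says.** Under Goals of This Study, CP alone means "women who have never experienced any form of psychological, physical, or sexual violence at any stage of their lives", whoever the perpetrator. Phase 2, Participants, carries this over: group 1 is "those who have CP and have never experienced IPV or any other type of violence (group 1"). The other two groups are "those who have CP and are currently experiencing IPV (group 2), or those who have CP and have a past history of IPV (group 3"). A woman counts as exposed to current or past IPV "if she reports experiencing any item more than once from the same partner", and no recall window is given.

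On age, the same Participants section states: "The reference population will include heterosexual women aged ≥18 years living in the province of Alicante". There is no upper limit. The phase 2 Procedure monitors recruitment weekly so that each group reaches its size. Age diversity is mentioned for the phase 1 interviews only.

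The phase 2 Data Analysis section names two-tailed "tests and ANOVA to compare means across groups", with no covariate. Age is collected as one of the risk and protective factors ("Age, belonging to a minority group (yes or no), years of education"). Table 2 marks sociodemographic characteristics for data analysis as well as for control purposes, but its footnote ties the control column to eligibility compliance.

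**The concern.** A whole-life criterion looks back over a few adult years for a woman of 20 and over five decades for a woman of 70. For any one woman, never-exposed status can be lost but not regained. Past IPV, once it has happened, stays in her history. Selection into group 1 and group 3 therefore depends on age, in opposite directions, even if the yearly risk of violence is the same at every age.

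Age also bears on what is measured. The Introduction says that chronic pain is more prevalent and more burdensome in older adults. The Discussion expects more disabling pain, less exercise and lower physical functioning in the IPV groups. An older past-IPV group could show some of that pattern with no effect of IPV at all. The findings are meant to feed assessment and intervention guidelines, so the distinction matters.

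**Working it through.** **Group sizes.** The plan's own figure comes first, because its group sizes are used below. Inputs from Sample Size Calculation: prevalence ratio 2.0, prevalence 20% (read as the rate in unexposed women, so 20% v 40%), 30% exposed, α 5% two-sided, power 90%. The two-proportion formula with allocation 0.3/0.7 gives 176.5 unexposed, and 192.8 with the continuity correction, hence 193. Then 192.8 × 3/7 = 82.6, hence 83 exposed. A second exposed group of 83 gives 193 + 83 + 83 = 359, as stated. Age plays no part in this calculation.

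**What the definitions imply.** Group 1 (never any violence) and group 3 (past IPV) are lifetime states. Group 2 (current IPV) is a present state and need not be older than group 1. The argument is therefore strongest for group 3 versus group 1.

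**Illustration 1: constant risk.** The documents give no age distribution, no incidence of violence by age and no age-outcome correlation, so all of these are assumptions.
- P(violence-free at age a) = exp(−h(a − 10)), with h = 0.005, 0.01 and 0.02 per year.
- Ages uniform over 18–80 (SD 17.9): the ever-exposed are older by 9.2, 10.2 and 12.2 years.
- Ages uniform over 25–75 (SD 14.4): older by 5.8, 6.4 and 7.7 years.
- Standardised gap: from 5.8/14.4 = 0.40 to 12.2/17.9 = 0.68.

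With no true IPV effect and age-outcome correlation r, the spurious difference is d = r × standardised gap. At 193 v 83 the standard error of d is √(1/193 + 1/83) = 0.131. The two-sided rejection rate is Φ(d/0.131 − 1.96) + Φ(−d/0.131 − 1.96).
- Low end: r = 0.2, d = 0.2 × 0.40 = 0.08, d/0.131 = 0.61, rejection 9%.
- High end: r = 0.3, d = 0.3 × 0.68 = 0.20, d/0.131 = 1.56, rejection 34%.

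**Illustration 2: other assumptions, ages 18–80.**

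| Assumption about first exposure | Ever-exposed minus never-exposed, mean age |
|---|---|
| Constant 0.5–3% per year from birth or from age 16, no cohort trend | +7.7 to +16.4 years |
| 2% or 4% per year, only from 16 to 25, 30 or 40, no cohort trend | +1.7 to +8.4 years |
| As the row above, with risk 1–2% lower per year of current age | −4.8 to +3.7 years |

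At a gap of 1.7 years, with age SD 14 and r = 0.2, d = 0.2 × 1.7/14 = 0.024 and the rejection rate is 5.4%, close to nominal.

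**Limit of both illustrations.** They compare never with ever any violence, which is not a planned contrast. Women exposed only to non-partner violence fit none of the three phase 2 groups, yet they are counted here among the exposed. The figures show the mechanism and do not predict the age gap between group 3 and group 1.

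**The case against.** The strongest reply is that the age gap is unknown. A reader might infer from the lifetime definition that the groups must differ in age, with the IPV groups older. The documents do not support that. If first exposure is concentrated early in life, or older cohorts report less, the gap can be near zero or reversed. Recruitment through different kinds of organisation can also move it either way. This reply stands, and it limits the point to a likely imbalance of unknown size and sign.

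Second, this is a condensed article, and a full analysis plan could name covariates. Age is collected and marked for analysis, and it may enter the feature ranking and classifiers. That is fair as far as it goes. But the article does name a method for comparing means, and that method is unadjusted. Using age as a classifier input does not adjust those contrasts. It may also let age rank as a profile feature partly because of how the groups were defined.

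Third, the aim is descriptive profiling, and Limitations calls the work preliminary and concedes that nonprobability sampling may introduce bias. This lowers the stakes. The Discussion nevertheless states directional hypotheses about the IPV groups, and an unadjusted difference cannot separate those from age.

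**Conclusion.** The point holds in a limited form. Two of the three groups are lifetime states, nothing stated for phase 2 balances age, and the named mean comparisons carry any age difference into the IPV contrasts. Past IPV versus CP alone is the contrast most at risk; the case is weaker for current IPV.

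The documents fix neither the size nor the direction. The scenarios tried give gaps from about −5 to +16 years, zero included. The 9% to 34% rejection rate is one illustration only. It needs a constant yearly risk, no cohort trend and an age-outcome correlation of 0.2 to 0.3, and should not be quoted as the expected error rate. The case for changing the analysis does not depend on it: an imbalance in either direction passes through an unadjusted comparison, and removing it costs almost nothing.

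**What to change.** In the phase 2 Data Analysis section, replace the unadjusted t tests and ANOVA for the group contrasts with ANCOVA or linear models containing group and age, and with generalised linear models containing the same terms for binary, ordinal or count outcomes. Report the age distribution of each of the three groups, so that readers can see the imbalance and how far the age ranges overlap. Optionally, report classifier performance beside a model using age alone.

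The cost is a change of analysis wording. Age is already collected, and the design and the stated 359 are unchanged. Age quotas in recruitment are not part of this recommendation: they would add a constraint to a sample that Limitations already describes as hard to reach, and the adjustment does not need them.

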#### Procedure

First, we will reach out to the organizations through which we plan to access both groups and request their collaboration. To contact women who have experienced or are experiencing IPV and women with CP, we will consult associations and support centers for IPV against women, CP associations, CP units, and primary health care centers. These organizations will be asked to inform their patients about the project and encourage their participation.

Eligible candidates will be required to complete a series of questionnaires (refer to the Instruments subsection) to determine whether they meet the inclusion and exclusion criteria. The data from those who do not meet the criteria will be discarded. Those who qualify will proceed to complete additional questionnaires. The answers from these questionnaires will help us form the 2 groups while ensuring diversity based on age, racial background, and degree of disabling CP.

The inclusion criteria for both groups will be as follows: (1) women aged ≥18 years, (2) in a heterosexual intimate relationship for at least 1 year (as per Spanish law, IPV against women pertains to violence perpetrated by male intimate partners) [15], and (3) living with a CP condition highly prevalent in women and among those who have experienced IPV against women (eg, fibromyalgia, abdominal pain, genitourinary tract pain, pelvic and genital pain, headaches [including migraines], back and neck pain, and chronic fatigue syndrome) [19-22]. Women belonging to group 1 will, in addition, have to be currently experiencing IPV.

The exclusion criterion for group 2 will be having previously experienced IPV against women or any other form of violence because this may affect their current intimate relationships. The exclusion criterion for both groups will be experiencing oncological pain.

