### Possible Traumatic Events Experienced: Adapted Version of Life Events Checklist for DSM-5

The original version of this checklist [128] contains 17 items referring to different stressful events. Participants will have to mark whether they have experienced, witnessed, or learned about each event; whether it was part of their job; or whether it does not apply to them. The adapted version will rephrase the items on physical and sexual assault (items 6 to 9) into a single item: exposure to “psychological, physical, and/or sexual violence or abuse at any stage of your life by a known or unknown person other than an intimate partner.”

The purpose of using this instrument is helping to control for any external traumatic events (eg, natural disasters) that may influence pain experiences different from experiencing IPV.

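### Lifetime non-partner violence bars a woman from the CP-alone group but not from either IPV group, so each planned IPV-versus-CP-alone comparison mixes IPV with other violence

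*Protocol article*

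**What the plan says.** **Comparator.** Under Goals of This Study, CP alone means "women who have never experienced any form of psychological, physical, or sexual violence at any stage of their lives", whoever the perpetrator was. The stated reason is "We include other forms of violence beyond IPV against women because they may also influence CP management and health outcomes". The phase 2 Participants section repeats the definition: "those who have CP and have never experienced IPV or any other type of violence (group 1").

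**IPV groups.** The same section defines the other two groups by partner violence only: "those who have CP and are currently experiencing IPV (group 2") and "those who have CP and have a past history of IPV (group 3"). Neither carries a condition on violence from other people.

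**Exclusions.** The phase 2 Procedure refers back to the criteria in the phase 1 Procedure. There the group numbers differ, and group 2 is the CP-alone group: "The exclusion criterion for group 2 will be having previously experienced IPV against women or any other form of violence". The only exclusion that applies to IPV women as well is a different one: "The exclusion criterion for both groups will be experiencing oncological pain".

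**Measurement.** The adapted Life Events Checklist merges the assault items into one question on lifetime violence from anyone other than a partner. Its purpose is given as "helping to control for any external traumatic events (eg, natural disasters) that may influence pain experiences different from experiencing IPV". Table 2 marks the checklist for both control and data analysis.

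**Analysis.** The phase 2 Data Analysis section names t tests and ANOVA for group means, then feature ranking and machine learning classifiers. It describes no restriction, stratification or adjustment on the non-partner item.

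**The concern.** The protocol accepts that non-partner violence can act on the outcomes, then removes it from one side of the comparison only. Any share of IPV women who also had other violence adds its effect to the group difference. A reader of the t test or ANOVA would credit that part to IPV.

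Two uses of the results are exposed. The first is the profile comparison itself, where a difference from CP alone could come from IPV, from other violence, or from both. The second is detection of IPV in health care, which the Abstract gives as a possible benefit. The non-partner item is 'no' for every CP-alone woman by construction. If it enters feature ranking or a classifier, it will help to separate the groups for a reason that lies in the recruitment rule. Women with CP, non-partner violence and no IPV also fit none of the three groups, so a classifier would never be tested on them.

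**Working it through.** **1. The plan's group sizes.** Inputs from Sample Size Calculation: 20% prevalence of the pain-avoidance pattern, prevalence ratio 2.0 (so 40% in the exposed), 30% exposed (3 exposed to 7 unexposed), alpha 5%, power 90%. Read as a two-sided comparison of 20% with 40% with continuity correction, this gives 193 unexposed and 83 exposed. A second IPV group of 83 gives 193 + 83 + 83 = 359, the stated total. The group sizes reproduce, and the point does not rest on them.

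**2. The built-in difference.** Let q be the share of IPV women with non-partner violence and s its effect on an outcome in SD units. The documents give neither, so both are assumptions. With no IPV effect:

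- expected difference, IPV minus CP alone = q × s
- SE at 193 versus 83 = √(1/193 + 1/83) = 0.131 SD
- rejection probability (two-sided 5%) = Φ(qs/SE − 1.96) + Φ(−qs/SE − 1.96)

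| q | s (SD) | q × s (SD) | Rejection probability |
|---|---|---|---|
| 20% | 0.2 | 0.04 | 6% |
| 40% | 0.2 | 0.08 | 9% |
| 60% | 0.2 | 0.12 | 15% |
| 20% | 0.5 | 0.10 | 12% |
| 40% | 0.5 | 0.20 | 33% |
| 60% | 0.5 | 0.30 | 63% |

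The nominal rate is 5%.

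**3. The same on the planning scale.** If non-partner violence has prevalence ratio r for the outcome and IPV has none, the apparent ratio is 1 + q(r − 1). For q = 0.2 and r = 1.25 this is 1.05. For q = 0.5 and r = 2.0 it is 1.50. An observed ratio equal to the planned 2.0 would then contain an IPV part of 2.0/1.05 = 1.90 or 2.0/1.50 = 1.33, on a multiplicative reading.

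**4. Can the recorded item separate the two?** Write V for non-partner violence and take CP alone against one IPV group. Three cells are filled: CP alone with V = 0, IPV with V = 0, and IPV with V = 1. In the additive model y = a + b·IPV + c·V their means are a, a + b and a + b + c. That is three parameters for three cells, so b is identified: b = mean(IPV, V = 0) − mean(CP alone). This equals the contrast restricted to IPV women without non-partner violence. The empty cell (no IPV, V = 1) means that the effect of other violence in women without IPV cannot be estimated.

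**5. Cost of restricting.** Power for 20% versus 40% against 193 comparators, with continuity correction:

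| IPV women removed | Left of 83 | Power |
|---|---|---|
| none | 83 | 0.90 |
| 20% | 66 | 0.85 |
| 30% | 58 | 0.81 |
| 50% | 42 | 0.71 |

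**The case against.** The strongest reply is that non-partner violence is already measured, in an item of its own, by an instrument meant to help control for events other than IPV and marked for data analysis. How it enters a model is detail that a journal article may leave to an analysis plan not shown. The phase 2 aim is also modest: to see whether three groups have distinct profiles, in what the Limitations call a preliminary study with nonprobability sampling.

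Much of this stands. The remedy's input is in hand, and a deliberately violence-free comparator is a legitimate choice. But the one-sided group definition is fixed in this document, and the comparisons it names are unadjusted, so the meaning of those contrasts is a matter for the protocol.

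A reader might infer more than the documents support:

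- *That no analysis could separate IPV from other violence.* Step 4 of the working shows otherwise. The item varies within the IPV groups, and the adjusted IPV coefficient is estimable.
- *That every group contrast is affected.* Current versus past IPV is not, because neither group is restricted.
- *That the study has committed itself to IPV as the explanation.* The sentence in Limitations that comes closest concerns a possible later extension to other regions and countries, and is conditional on finding little difference between them.
- *That women with CP, other violence and no IPV are common, and that their phase 2 records will be deleted.* No prevalence is given, and deletion of ineligible records is stated for phase 1 only.

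**Conclusion.** The concern holds for the comparisons of CP alone with current IPV and with past IPV. The phase 1 groups have the same one-sided rule. As named, the t tests and ANOVA estimate the difference between IPV with or without other violence and no violence of any kind, and a result should not be reported as the effect of IPV alone.

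The size is unknown. Over the assumed range it runs from negligible (0.04 SD, 6% rejection) to serious (0.30 SD, 63%), and the upper end needs both a high share and a large effect of other violence. The calculation assumes equal SDs, no IPV effect and no other confounding. What the design leaves out is narrower than it may seem: it has no women with other violence and no IPV, but it does hold the data for a like-for-like IPV contrast. This is a point that should be corrected; it does not invalidate the study.

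**What to change.** 1. State that each IPV-versus-CP-alone contrast will be reported twice: once as now planned, and once with the IPV group restricted to women who report no personal experience of non-partner violence on the checklist item. Adjusting for the item in an additive model gives the same estimate.
2. Read the restricted result by its estimate and interval. Do not make significance in the smaller set a condition for attributing a difference to IPV, because a true difference would often be missed there.
3. Describe the unrestricted contrast as IPV with or without other violence versus no violence.
4. Leave the non-partner item out of feature ranking and of the classifiers that separate CP alone from IPV.
5. Optionally, keep phase 2 responses from women with CP and non-partner violence but no IPV as a separate descriptive group that does not count toward the 193.

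**Cost.** Items 1 to 4 need no new question and leave the 193/83/83 recruitment unchanged. The price is precision in the restricted set, as tabulated in step 5 of the working. Restoring 83 per IPV group after restriction would need 83/(1 − q) women in each: about 104 if 20% are removed, or 166 if 50% are. I would accept the wider intervals and leave the sample size alone. Item 5 has to be settled before those women are turned away, since their answers cannot be recovered later.
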